### Assignment of interventions: allocation

#### Sequence generation {16a}

Participants will be randomized to either MBT-early or CBT using a computerized 1:1 allocation sequence generated by an independent statistician. Randomization will be blocked with random permuted blocks of sizes 4, 6, and 8.

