## Methods: participants, interventions, and outcomes

### Study setting {9}

Three mental healthcare institutions in the Netherlands participate in this study: Mentaal Beter (Bergen op Zoom, Roosendaal, Etten-Leur, and Breda), GGz Breburg (Breda), and de Viersprong (Bergen op Zoom). All three of these institutions provide treatments for young people referred for (emerging) mental health problems and offer interventions for a wide range of mental health problems. GGz Breburg provides both MBT-early and CBT, while Mentaal Beter only provides CBT and de Viersprong solely provides MBT-early. Consequently, adolescents referred to Mentaal Beter and randomized to MBT-early will receive treatment administrated by therapists from de Viersprong, while those referred to de Viersprong and randomized to CBT will be treated at Mentaal Beter.

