#### Concealment mechanism {16b}

Participants are randomized by an independent researcher, following a password-protected computer list with the 1:1 allocation sequence. Allocation will be only revealed to the adolescent, therapist and trial coordinator upon randomization by the independent researcher. The research assistants will not be informed about the allocation.

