#### Implementation {16c}

After informed consent is provided and baseline assessment has taken place, an independent researcher will generate the allocation and inform the trial coordinator about the result. To keep the research assistants blind for the allocation, the trial coordinator directly informs the adolescent (and parents) and therapist about the assigned treatment.

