## Statistical methods

### Statistical methods for primary and secondary outcomes {20a}

Data analysis will be conducted using SPSS Statistics. Treatment outcomes of the primary outcome, severity of BPD symptoms, over time will be examined using multilevel modelling. Multilevel modelling is able to model data from different time points, correcting for the dependency of observations by adding a within-subject correlation structure to the regression model. Another advantage of multilevel modelling is that it is able to handle missing data, by using the available data irrespective of the number of repeated measurements. In other words, adolescents with an incomplete number of follow-up measurements are also included in the treatment outcome analyses.

The interventions will be compared with the intention-to-treat adolescent sample, that is, with all adolescents randomized to either MBT-early or CBT.

A deviance test using restricted maximum likelihood will be used to assess whether random or fixed slopes should be assumed in models for each outcome variable. Subsequently, time will be included as appropriate (i.e. linear, logarithmic) and included in the model together with the treatment group and time by group interactions if likelihood ratio tests show significant improvement. The primary effect size of the treatments will be estimated from baseline to end of treatment and secondary effect sizes from baseline to 12-, 18-, and 24-month follow-up. Additional treatment offered in the follow-up period will be included as a covariate in the estimation of the multilevel models and effect sizes from baseline to 12-, 18-, and 24-month follow-up, as well as a predictor of treatment outcomes at 12-, 18-, and 24-month follow-up.

The secondary outcomes will be analysed similarly using multilevel modelling, in which the type of model is adapted to the outcome if needed (i.e. binary in case of the C-SSRS) from baseline to end of treatment, 12-, 18-, and 24-month follow-up. As noted, additional treatment offered in the follow-up period will be included as a covariate in the estimation of the multilevel models and effect sizes from baseline to 12-, 18-, and 24-month follow-up, as well as a predictor of treatment outcomes at 12-, 18-, and 24-month follow-up.

To examine the possible influence of missing data, we will repeat the analyses described using datasets in which missing data are imputed with state-of-the-art data imputation methods [66].

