### Methods for additional analyses (e.g. subgroup analyses) {20b}

N/A. There are no additional analyses planned.

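### At two of the three institutions the allocated arm decides whether the patient changes provider; the described analysis neither shows this nor uses referring institution to regain precision

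*Protocol article*

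**What the plan says.** **Who delivers what.** Study setting {9} states: "GGz Breburg provides both MBT-early and CBT, while Mentaal Beter only provides CBT and de Viersprong solely provides MBT-early". It follows that "adolescents referred to Mentaal Beter and randomized to MBT-early will receive treatment administrated by therapists from de Viersprong", whereas "those referred to de Viersprong and randomized to CBT will be treated at Mentaal Beter".

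**Allocation.** Sequence generation {16a} describes a computerised 1:1 sequence and adds: "Randomization will be blocked with random permuted blocks of sizes 4, 6, and 8". No stratification factor is named. Concealment mechanism {16b} has patients randomised "following a password-protected computer list with the 1:1 allocation sequence"; separate lists per institution are not mentioned. On timing, Implementation {16c} says: "After informed consent is provided and baseline assessment has taken place, an independent researcher will generate the allocation".

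**Analysis.** Statistical methods {20a} describes a multilevel model in which time is "included in the model together with the treatment group and time by group interactions if likelihood ratio tests show significant improvement". The only covariate named is additional treatment received during follow-up. Referring institution does not appear. The section on additional analyses {20b}, which covers subgroup analyses among others, says: "There are no additional analyses planned".

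**The concern.** Two separate issues arise.

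**Change of provider.** A Mentaal Beter referral keeps the referring institution as provider if allocated CBT and changes provider if allocated MBT-early. For a de Viersprong referral the reverse holds. Within each of these institutions, the change coincides completely with one arm. If changing provider shortly after intake and baseline has any effect on outcome, that effect is inside the treatment difference. A reader who takes the result as the effect of one therapy against the other would attribute it to the therapy.

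**Chance imbalance.** Blocking a single unstratified list keeps the arm totals close to equal, but does not do so within institutions. If the institutions' patients differ in prognosis, the model as described leaves that variation in the error, although referring institution is known for every patient before randomisation.

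The trial is planned around d = 0.50, so a shift of one or two tenths of an SD would matter for interpretation.

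**Working it through.** **Inputs from the protocol article.** Target of 132 patients, 66 per arm; 59 per arm with at least one follow-up; d = 0.50; two-sided alpha 0.05 (Sample size {14}). Permuted blocks of 4, 6 and 8 ({16a}). Provider arrangement as in Study setting {9}.

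**Inputs not given, hence assumed.** Referral shares of Mentaal Beter (p_M) and de Viersprong (p_V); effect tau of changing provider, taken as a loss of 0.1 to 0.3 SD; prognostic gap between institutions, taken as 0.5 SD.

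**1. Who changes provider.**

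| Referred to | Allocated CBT | Allocated MBT-early |
|---|---|---|
| Mentaal Beter | no change | de Viersprong therapists |
| de Viersprong | treated at Mentaal Beter | no change |
| GGz Breburg | available there | available there |

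The expected share changing provider is therefore p_M in the MBT-early arm and p_V in the CBT arm.

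**2. Shift in the treatment contrast.** Shift against MBT-early = tau × (p_M − p_V). Power is for two means at 59 per arm, normal approximation: Φ((0.5 − shift)/√(2/59) − 1.96). This benchmark gives 77.5% with no shift. It is an unadjusted yardstick, not the plan's own 80% calculation, which is not at issue here.

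| p_M / p_V | Shift for tau 0.1 to 0.3 | Power at 59 per arm |
|---|---|---|
| 33% / 33% | 0 | 77.5% |
| 50% / 25% | 0.025 to 0.075 SD | 73% to 64% |
| 70% / 10% | 0.06 to 0.18 SD | 67% to 41% |
| 80% / 5% | 0.075 to 0.225 SD | 64% to 32% |

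If de Viersprong refers more than Mentaal Beter, the sign reverses and the shift favours MBT-early. If changing provider helps rather than harms, it reverses again.

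**3. Can stratification or a covariate remove this?** No. Within Mentaal Beter, every MBT-early patient changes provider and no CBT patient does; within de Viersprong it is the other way round. Conditioning on institution leaves arm and change fully aligned. Only GGz Breburg offers a contrast without a between-institution change.

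**4. Chance imbalance in referring institution.** Suppose an institution contributes 26 of 132 patients. With 66 per arm in total, the number of them in one arm is hypergeometric (132, 66, 26), mean 13, SD √(26 × 0.25 × 106/131) = 2.29. P(9 or fewer, or 17 or more) = 0.124. Simulating one list with blocks of 4, 6 and 8 gives 0.125 to 0.13. Independent coin tosses would give 0.169, but that ignores the blocking.

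In simulated lists with p_M of 33%, 50% or 70%, the between-arm difference in Mentaal Beter share averages zero, has SD 7.7 to 8.8 percentage points and a 95% range of about ±15 to 17 points. It exceeds 10 points in 20% to 26% of trials. With a 0.5 SD gap between institutions this is about 0.5 × 0.16 = ±0.08 SD of random error, centred on zero.

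**5. What adjustment buys.** If institution explains 2%, 5% or 10% of outcome variance, the unadjusted requirement of 62.8 per arm becomes 61.5, 59.7 or 56.5. Power at 59 per arm goes from 77.5% to 78.3%, 79.6% or 81.7%. The gain is small.

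**6. Precision of the GGz Breburg estimate.** If it refers 26 patients, 13 per arm, the standard error is √(2/13) = 0.39 SD, so the 95% half-width is 1.96 × 0.39 = 0.77 SD. It can aid interpretation but cannot settle the question.

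**The case against.** The case against is substantial, and parts of it stand.

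- **Referral population is not a confounder.** A reader might infer that unstratified allocation mixes the treatment effect with differences between referral populations. It does not. Patients are randomised after referral, screening, consent and baseline, so referral mix is balanced in expectation, and the usual error rates already allow for chance imbalance. This stands in full.
- **Missing stratification does not cause the mixing with provider change.** It is tempting to join the two issues with a therefore. The alignment comes from the provider arrangement in Study setting {9} and would remain under any randomisation scheme or covariate set. This also stands.
- **A physical move is only partly documented.** For de Viersprong referrals allocated to CBT, treatment at another institution is stated. For Mentaal Beter referrals allocated to MBT-early, the text says only whose therapists deliver it. Extra waiting, a second intake or a higher chance of not starting are not in the protocol. Nor does it say that patients who stay keep the same clinician.
- **The section on additional analyses does not close everything.** It answers the reporting item on subgroup and similar analyses; imputation analyses are still planned elsewhere. Even so, it leaves out the look at the effect by institution that this provider arrangement calls for.
- **Unstratified blocking is valid, and covariates may be left to an analysis plan.** True. An intention-to-treat comparison of the treatments as delivered is also coherent. But the article does describe the model and its one covariate, and says no additional analyses are planned. An inexpensive improvement remains available.

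**Conclusion.** The point holds in limited form. At Mentaal Beter and de Viersprong, the arm determines whether the provider changes, so any effect of that change is part of the contrast there. Its net contribution is zero if the two institutions refer equal shares and grows with the difference between them. Under the assumed losses of 0.1 to 0.3 SD it ranges from 0 to about 0.2 SD. The protocol supplies neither the shares nor the effect, so size and direction cannot be fixed. The stronger reading, that the trial is confounded by referral population or that stratifying would have cured the problem, is not supported.

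Separately, referring institution is neither a stratum nor a model term as described. The consequence is modest lost precision from chance imbalance, with a probability of about 0.12 of a 9:17 split or worse for an institution of 26 patients. It is worth correcting because the correction is inexpensive and the information is already held.

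**What to change.** 1. In Statistical methods {20a}, add referring institution as a fixed effect in the primary and secondary models. If baseline is modelled as one of the repeated outcomes, a main effect adjusts level only; institution by time would be needed to adjust the change, at two further degrees of freedom per time term.
2. In the section on additional analyses {20b}, replace the statement that none is planned with one pre-specified supportive analysis: the treatment effect by referring institution, with the GGz Breburg estimate shown separately and labelled as imprecise and for interpretation only.
3. Report, by arm and referring institution, how many patients changed provider.
4. State that the main result compares the two treatments as delivered in this setting, including the change of provider where it occurs.
5. Stratify the list by referring institution only for any patients still to be randomised. Recruitment was expected to finish by the third quarter of 2024, so this may no longer apply.

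**Cost:** two degrees of freedom for the main effect, a little extra analysis and some wording. No new data are needed, and the sample size is unaffected. Items 1 and 2 should be fixed before outcomes are analysed.

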#### Concealment mechanism {16b}

Participants are randomized by an independent researcher, following a password-protected computer list with the 1:1 allocation sequence. Allocation will be only revealed to the adolescent, therapist and trial coordinator upon randomization by the independent researcher. The research assistants will not be informed about the allocation.

#### Implementation {16c}

After informed consent is provided and baseline assessment has taken place, an independent researcher will generate the allocation and inform the trial coordinator about the result. To keep the research assistants blind for the allocation, the trial coordinator directly informs the adolescent (and parents) and therapist about the assigned treatment.

### Assignment of interventions: blinding

#### Who will be blinded {17a}

Research assistants are kept blind for the treatment allocation. The trial coordinator, adolescent (and parents), and therapist will not be blinded but are strongly inculcated to not disclose the assigned treatment during end-of-treatment assessment and follow-up assessments. To check whether research assistants are still blinded for the assigned treatment during the study, research assistants are asked after each assessment to which treatment the adolescents was allocated.

#### Procedure for unblinding if needed {17b}

N/A. Only research assistants will be blinded. There is no need to unblind research assistants, as the trial coordinator, participants, and therapists are all not blind in this trial.

### Data collection and management

#### Plans for assessment and collection of outcomes {18a}

To assess the primary outcome, semi-structured interviews will be administered by trained research assistants at baseline, end of treatment and at 24-month follow-up. To assess the secondary outcomes, questionnaires will be collected through the online database BergOp (https://www.bergop.info), to minimize data entry errors. For a detailed description of the instruments used in this trial, see the ‘Outcomes {12}’ section. For the administration of the BPDSI-IV-ado and C-SSRS, research assistants will be trained and supervised by senior researchers. The research assistant writes a report on the results of the BPDSI-IV-ado and, if requested, provides this report to the adolescent.

All data will be anonymized and saved in a folder on a secured server of ‘de Viersprong’, which can only be accessed by the research team. The data will be stored, coded, and cleaned before analyses (e.g. checking for duplicates, coding of missings and date of entry) in SPSS.

#### Plans to promote participant retention and complete follow-up {18b}

Research assistants will follow and motivate adolescents for the assessments during the study. To limit the burden related to follow-up, questionnaires are provided through an online program, and semi-structured interviews will only be administered at the end of treatment and 24-month follow-up. Adolescents have the opportunity to do the interviews at the location or through video conference. Travel expenses will be refunded and adolescents receive a small gift (with a value of €15) after every completed assessment.

Adolescents are allowed to refuse to participate in an assessment and are not obliged to give a reason for not participating. They will be invited for the next assessment planned unless they withdraw their consent for participating in the study. Adolescents may withdraw from the trial at any time for any reason, without any consequences (i.e. they can complete their assigned treatment) and will not be contacted for further assessments.

#### Data management {19}

Every adolescent receives a unique key code, not based on their initials, birthdate or medical record. In the data files, used for monitoring inclusion and data collection, and for the statistical analyses, only the unique key code of each adolescent will be used and no personal identifiable data. The identification code list that connects adolescents with the research data is encrypted and only available to the research team.

Questionnaires will be administrated online through BergOp (https://www.bergop.info), and the results are stored in SPSS. The output of the interviews is also kept in SPSS, and the written reports are stored in a secured folder. Any data on paper (e.g. scoring forms) is stored in a locked room at de Viersprong. All data stored in a secured folder on the network of de Viersprong can only be accessed by the research team. All changes made to the raw data and steps taken in the analyses will be kept in a logbook.

#### Confidentiality {27}

As stated under the ‘Data management {19}’ section, in the research data only the unique key code will be used and no personal identifiable data. Only the research team can store, manage, and access the research data. No personal identifiable data will be reported in publications. Data will be stored for 15 years at de Viersprong, according to the Medical Ethical Committee guidelines.

#### Plans for collection, laboratory evaluation, and storage of biological specimens for genetic or molecular analysis in this trial/future use {33}

N/A. No biological specimens will be collected or stored in this study.

## Statistical methods

### Statistical methods for primary and secondary outcomes {20a}

Data analysis will be conducted using SPSS Statistics. Treatment outcomes of the primary outcome, severity of BPD symptoms, over time will be examined using multilevel modelling. Multilevel modelling is able to model data from different time points, correcting for the dependency of observations by adding a within-subject correlation structure to the regression model. Another advantage of multilevel modelling is that it is able to handle missing data, by using the available data irrespective of the number of repeated measurements. In other words, adolescents with an incomplete number of follow-up measurements are also included in the treatment outcome analyses.

The interventions will be compared with the intention-to-treat adolescent sample, that is, with all adolescents randomized to either MBT-early or CBT.

A deviance test using restricted maximum likelihood will be used to assess whether random or fixed slopes should be assumed in models for each outcome variable. Subsequently, time will be included as appropriate (i.e. linear, logarithmic) and included in the model together with the treatment group and time by group interactions if likelihood ratio tests show significant improvement. The primary effect size of the treatments will be estimated from baseline to end of treatment and secondary effect sizes from baseline to 12-, 18-, and 24-month follow-up. Additional treatment offered in the follow-up period will be included as a covariate in the estimation of the multilevel models and effect sizes from baseline to 12-, 18-, and 24-month follow-up, as well as a predictor of treatment outcomes at 12-, 18-, and 24-month follow-up.

The secondary outcomes will be analysed similarly using multilevel modelling, in which the type of model is adapted to the outcome if needed (i.e. binary in case of the C-SSRS) from baseline to end of treatment, 12-, 18-, and 24-month follow-up. As noted, additional treatment offered in the follow-up period will be included as a covariate in the estimation of the multilevel models and effect sizes from baseline to 12-, 18-, and 24-month follow-up, as well as a predictor of treatment outcomes at 12-, 18-, and 24-month follow-up.

To examine the possible influence of missing data, we will repeat the analyses described using datasets in which missing data are imputed with state-of-the-art data imputation methods [66].

To investigate the cost-effectiveness of MBT-early compared to CBT, an economic evaluation will be performed using a ‘piggyback economic evaluation’, which means that health economic data will be collected alongside the clinical trial and will be analysed using the same time horizon as the trial. The economic evaluation will be performed from a societal perspective, and all analyses will be conducted according to the intention-to-treat principle, in which we adhere to the related guidelines [67–69]. For example, parameter uncertainty will be covered by, for example, sensitivity analyses in which imputed uncertainty is also taken into account by repeating the economic evaluation on the imputed dataset and sampling uncertainty will be taken into account by providing a cost-effectiveness acceptability curve and frontier [67].

To investigate the potential differences between the adolescents in the MBT-early group and the adolescents in the CBT treatment group, parametric and nonparametric descriptive statistics will be used, as appropriate.

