**Intensive treatment phase**

The intensive treatment phase consists of an assessment phase (3–4 sessions), a middle phase (10 sessions), and a final phase (2 sessions). The sessions include 16 individual sessions, 3 family sessions, 2 treatment review sessions, and, if necessary, psychiatric consultations and case management (e.g. consultation with school). These treatment modalities are delivered by 1 therapist, and interventions are tailored to the specific needs of the adolescent and his/her family (e.g. case management may partially replace individual sessions if problems manifest primarily at school). However, this standard package can be downscaled in cases of rapid improvement or upscaled when needed.

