##### Strategies to improve adherence to interventions {11c}

Both the CBT and MBT-early teams consist of therapists with broadly ranging level of experience, background, and educational level. All therapists involved in the study are certified psychologists, sociotherapists, remedial educationalists, or psychotherapists. Clinicians within the CBT teams who are involved in the study have successfully completed a certified CBT basic course or are further trained in CBT. CBT therapists have weekly one-on-one supervision to review case material with their supervisor. MBT-early therapists who are involved in the study have successfully completed a certified MBT basic course at the minimum or are further trained in MBT. Within the MBT-early programme, biweekly team supervision focuses on reviewing case material to increase therapists’ comprehension of mentalizing theory and their competency in working with the principles of MBT and the spectrum of mentalizing interventions. In order to test for adherence, ten randomly selected individual sessions of both CBT as well as the MBT-early will be scored on an, for the treatment appropriate, adherence scale.

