### Sample size {14}

The sample size is determined by the predicted difference between the groups on the primary outcome, the BPDSI-IV-ado [46]. Consistent with previous studies on MBT for adolescents [43, 64] and MBT for adolescents compared with treatment as usual [27], we expect a medium effect size (Cohen’s *d* = 0.50) difference between MBT-early and CBT. Based on the BPDSI-IV-ado and with a two-sided *α* = 0.05, a power of 0.80 and a correlation of 0.50 between the repeated measures, based on Bales et al. [65] and Hutsebaut et al. [43], we require 59 participants in each treatment group (118 in total) with at least 1 follow-up measurement. Because of the vulnerable and unpredictable target population, we anticipate a 10% attrition rate and therefore intend to recruit at least 66 participants per group.

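### Neither the described multilevel model nor the sample size allows for clustering by therapist; with any positive therapist correlation the standard error is understated and power falls

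*Protocol article*

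**What the plan says.** **Model.** Protocol article, Statistical methods {20a}: the multilevel model handles data from several time points, "correcting for the dependency of observations by adding a within-subject correlation structure to the regression model". The terms then listed are random or fixed slopes, time, treatment group and time by group. The primary effect runs from baseline to end of treatment. No therapist or centre level is named.

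**Sample size.** Sample size {14} assumes d = 0.50, two-sided alpha 0.05, and "a power of 0.80 and a correlation of 0.50 between the repeated measures". It concludes: "we require 59 participants in each treatment group (118 in total) with at least 1 follow-up measurement". The only inflation is for dropout: "we anticipate a 10% attrition rate and therefore intend to recruit at least 66 participants per group". There is no ICC, cluster size or design effect.

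**Delivery.** CBT is an individual, manualized treatment (Intervention description {11a}). For MBT-early, "These treatment modalities are delivered by 1 therapist". Section {11c} describes a CBT team and an MBT-early team, each made up of "therapists with broadly ranging level of experience, background, and educational level". Under Study setting {9}, Mentaal Beter gives CBT only, de Viersprong gives MBT-early only, and GGz Breburg gives both. Patients are sent across institutions according to their allocation.

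**The concern.** Patients of the same therapist tend to share part of their outcome, because therapists differ in skill, style and experience. Where each therapist works in one arm only, that shared part does not cancel between arms. It goes into the difference that the trial sets out to estimate. A within-subject level cannot absorb it, because it links observations of one patient and not patients of one therapist.

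An analysis that treats patients as independent then gives confidence intervals that are too narrow and rejects a true null too often. A sample size computed as if patients were independent promises more power than a valid analysis can deliver. This trial claims superiority on a single primary outcome, so a false positive in either direction is the main risk.

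**Working it through.** **1. Inputs from the protocol.** d = 0.50, two-sided alpha 0.05 (z = 1.960), power 0.80 (z = 0.842), repeated-measures correlation 0.50, 59 analysable per arm, 10% attrition.

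**2. The plan's own figure.** For a change score the variance factor is 2(1 − 0.50) = 1, so

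n = 2 × (1.960 + 0.842)² / 0.50² × 1 = 62.8, that is 63 per arm.

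The stated 59 is not reproduced. At 59 per arm, power for the change contrast is Φ(0.50 × √(59/2) − 1.960) = 77.5%. With adjustment for baseline the factor is 1 − 0.50² = 0.75, giving 48 per arm and 88.0% power at 59. The attrition step does reproduce: 59 / 0.9 = 65.6, so 66 per arm and 132 in total. The gap between 59 and 63 has nothing to do with therapists. To isolate the effect of clustering, steps 4 and 5 take the stated 80% at 59 per arm as given.

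**3. Inputs not in the documents.** Therapist ICC (on change from baseline) and patients per therapist, m. Both are assumed: ICC 0.01 to 0.05, m 4 to 12.

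**4. Formulas.**
- Design effect: DE = 1 + (m − 1) × ICC
- Type I error if clustering is ignored: 2 × [1 − Φ(1.960 / √DE)]
- Power of a test with the correct standard error: Φ(2.802 / √DE − 1.960), where 2.802 = 1.960 + 0.842
- Widening of the confidence interval: √DE − 1

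Worked case, ICC 0.05 and m = 8: DE = 1 + 7 × 0.05 = 1.35 and √DE = 1.162. Type I error = 2 × [1 − Φ(1.687)] = 9.2%. Power = Φ(2.411 − 1.960) = 67.4%.

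**5. Results.**

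| ICC | m | DE | Type I error | Power from stated 80% | CI wider by |
|---|---|---|---|---|---|
| 0.01 | 4 | 1.03 | 5.3% | 78.8% | 1.5% |
| 0.02 | 6 | 1.10 | 6.2% | 76.2% | 4.9% |
| 0.05 | 8 | 1.35 | 9.2% | 67.4% | 16% |
| 0.05 | 12 | 1.55 | 11.5% | 61.4% | 24% |

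The power formula uses normal quantiles. With few therapists a t reference would lower these figures further.

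**6. Dependence on the starting point.** For the same four cases, power at 59 per arm is 76.3%, 73.5%, 64.7% and 58.8% for an unadjusted change score. With baseline adjustment it is 87.1%, 84.8%, 77.0% and 71.2%. Type I error does not depend on this choice.

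**7. Check by simulation.** 20,000 null trials with 59 per arm, 8 therapists per arm (assumed) and ICC 0.05 on the change score gave a type I error of about 9% ignoring therapist and about 5% when therapist means were compared.

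**The case against.** The strongest reply has four parts.

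- **The model is only outlined.** The text explains what multilevel modelling can do and does not exclude a further level. The article is condensed, and an unseen analysis plan may add a therapist term. That is fair for the model, and such a term would correct the standard error. It would not restore the power stated under Sample size {14}, which is fixed there without any clustering allowance.
- **Nesting is partly inferred.** GGz Breburg provides both treatments, and nothing says that no therapist treats in both arms. For a therapist who does, shared variance partly cancels. The one-therapist statement covers MBT-early only. This stands, so the accurate description is largely nested.
- **Delivery is standardised.** Certified training, weekly CBT supervision, biweekly MBT-early supervision, adherence scoring and a CBT manual are all meant to reduce differences between therapists. They argue for a smaller ICC, not for zero.
- **The loss may be small or absorbed.** At ICC 0.01 with 4 patients per therapist it is about one point of power. A baseline-adjusted analysis would keep 80% power up to a design effect of about 1.25. But the plan describes change with time by group, not that adjustment, and spare power does not repair the type I error.

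A reader might infer that the standard error is certainly too small and that the trial's true power is one of the figures tabulated. The documents do not support that. They give no ICC, caseload or number of therapists, and the 80% starting point is itself not reproduced.

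**Conclusion.** The concern holds in conditional form. As described, the model and the sample size treat patients as independent of one another, although individual therapies are delivered by teams largely nested in arm. For any positive therapist ICC with more than one patient per therapist, the standard error is understated, type I error exceeds 5%, and power is below that of the unclustered calculation.

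How much is not known from the documents. Over the assumed range it runs from nearly negligible to serious. The power figures illustrate the loss from a nominal 80% and are not estimates of this trial's power. The direction is secure. The size depends on the assumed ICC and caseload and on how complete the nesting is.

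**What to change.** 1. Record the treating therapist for every patient in both arms, including any change of therapist.
2. Add a therapist-level random effect to the primary model that reaches the change contrast, such as a therapist-by-time effect. An intercept that is constant over time would cancel from change since baseline, and baseline is measured before a therapist is assigned. Nest the effect in arm, or cross it with arm for any therapist who treats in both.
3. Use Satterthwaite or Kenward-Roger degrees of freedom, and keep the term whatever its p-value.
4. Restate the power under Sample size {14} over a range of ICCs, for example 0.01 to 0.05, at the actual number of therapists and caseloads. Correct or explain the 59 per arm at the same time.

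**Cost.** Confidence intervals wider by about 1% to 24% over the range shown, an imprecise variance component if therapists are few, and a less favourable stated power. No extra patients or visits are needed to make the analysis valid. This does not recover the lost power: holding the nominal 80% at ICC 0.05 with 8 per therapist would take 59 × 1.35 = 79.7, so 80 analysable per arm, and 80 / 0.9 = 88.9, so 89 recruited per arm.
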